| NEUROLOGIC                     |                                                                                        |                                                                                                                           |                                                                                                                                                   |                                                                                              |
| Neuro-psych/mood                      | NA                                                                                     | Depression or anxiety symptoms causing individual to seek attention and be treated with counseling and/or pharmacotherapy | Severe mood changes requiring additional medical intervention
AND/OR
Suicidal ideation/gesture                                       | Suicidal attempt                                                                             |
| Paresthesia (burning, tingling, etc.) | Minimal discomfort resulting in minimal or no interference with ADL                    | Notable symptoms resulting in greater than minimal changes in ADL                                                         | Marked and persistent discomfort resulting in significant incapacity*
AND/OR
Narcotic analgesia required for symptomatic improvement | NA                                                                                           |
| Neuro-motor                           | Mild weakness resulting in minimal or no interference with ADL                         | Moderate weakness resulting in greater than minimal interference with ADL                                                 | Significant incapacity*                                                                                                                           | Paralysis
AND/OR
Respiratory muscle weakness resulting in ventilator dependence |
| Neuro-sensory                         | Mild impairment (decreased sensation) resulting in minimal or no interference with ADL | Moderate impairment resulting in greater than minimal interference with ADL                                               | Significant incapacity*                                                                                                                           | NA                                                                                           |
| Neuro-cerebellar                      | Slight incoordination
OR
Dysdiadochokinesia                               | Intention tremor
OR
Slurred speech
OR
Nystagmus                                                 | Ataxia requiring assistance to walk or arm incoordination interfering with ADL                                                                    | Unable to stand                                                                              |
| RESPIRATORY                    |                                                                                        |                                                                                                                           |                                                                                                                                                   |                                                                                              |
| Cough (for aerosol studies only)      | Transient resulting in minimal or no interference with ADL                             | Treatment-associated cough resulting in greater than minimal interference with ADL                                        | Uncontrolled cough causing significant incapacity*                                                                                                | NA                                                                                           |
| Bronchospasm Acute                    | Transient; no Rx; FEV1 or peak flow reduced to 70 - 80%                                | Rx required; normalizes with bronchodilator; FEV1 or peak flow 50 - 69%                                                   | No normalization with bronchodilator; FEV1 or peak flow < 49%; retractions                                                                        | Cyanosis or other symptoms requiring intubation and ICU hospitalisation                      |
| Dyspnoea                              | Dyspnoea on exertion (such as stairs)                                                  | Dyspnoea with normal activity (such as walking)                                                                           | Dyspnoea at rest                                                                                                                                  | Dyspnoea requiring oxygen therapy                                                            |

|                         | SEVERITY GRADING                                                                    |                                                                                                          |                                                                                                                   |                                                                                                              |
|-------------------------|-------------------------------------------------------------------------------------|----------------------------------------------------------------------------------------------------------|-------------------------------------------------------------------------------------------------------------------|--------------------------------------------------------------------------------------------------------------|
| PARAMETER               | MILD                                                                                | MODERATE                                                                                                 | SEVERE                                                                                                            | VERY SEVERE                                                                                                  |
| MISCELLANEOUS    |                                                                                     |                                                                                                          |                                                                                                                   |                                                                                                              |
| Arthritis               | NA                                                                                  | Any pain with inflammation, erythema, or joint swelling that interferes with ADL                         | Severe pain with inflammation, erythema, or joint swelling causing significant incapacity*                        | Associated with clinical diagnosis of a systemic autoimmune disease                                          |
| Eye                     | Symptoms resulting in minimal or no interference with ADL                           | Notable symptoms resulting in greater than minimal interference with ADL                                 | Symptoms (such as loss of vision, clinically diagnosed uveitis, or glaucoma) resulting in significant incapacity* | NA                                                                                                           |
| Skin (general)          | Scattered macular or papular eruption
OR
Erythema that is asymptomatic        | Scattered macular
OR
Papular eruption
OR
Erythema with pruritis or other associated symptoms | Generalized symptomatic macular, papular, or vesicular eruption                                                   | Exfoliative dermatitis
OR
Ulcerating dermatitis                                                        |
| Clinical adverse events | Awareness of sign or symptom but tolerated with minimal or no interference with ADL | Notable symptoms resulting in greater than minimal interference with ADL                                 | Symptoms causing significant incapacity*                                                                          | Significant intervention/therapy required; hospitalisation required to prevent permanent impairment or death |

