## 5.0 STUDY DESIGN AND ENDPOINTS

### 5.1 STUDY ENDPOINTS

#### 5.1.1 Primary Endpoints

Safety and Tolerability:

- Severe and very severe local reactogenicity events (pain, tenderness, erythema/skin discoloration, skin damage [vesiculation/ulceration], induration, formation of crust or scab)
- Severe and very severe systemic reactogenicity events (fever, chills, headache, nausea, vomiting, malaise, myalgia)
- Severe and very severe other adverse events (including laboratory abnormalities)
- All Serious Adverse Events
- Proportion of volunteers with mild and moderate local and systemic reactogenicity events and adverse events

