**Table 3**  
**Laboratory Parameters**

| Laboratory Parameter | Test                                                                                                                                                                              |
|----------------------|-----------------------------------------------------------------------------------------------------------------------------------------------------------------------------------|
| Hematology           | Full blood count, differential and platelet count                                                                                                                                 |
| Clinical chemistry   | Liver function tests: aspartate transferase (AST), alanine aminotransferase (ALT), total and direct bilirubin

Kidney function test: creatinine                             |
| Immunology:          | CD4 and CD8 T cells (percentage and absolute count); anti-double stranded DNA                                                                                                     |
| Urinalysis           | Dipstick: protein, blood, glucose, ketones, esterase (leukocytes), nitrite. If abnormalities are found on dipstick analysis for protein, blood, or leucocytes, perform microscopy |

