| Fever                                    | 37.7 – 38.6°C
99.8 – 101.5° F                                                                    | 38.7 – 39.3°C
101.6 – 102.7° F                                                                                                                                                                      | 39.4 – 40.5°C
>102.8 – 104.9° F                                                                                           | > 40.5°C
> 105° F                                        |
| Nausea                                   | Transient (< 24 hours) or intermittent symptoms resulting in minimal or no interference with intake | Persistent symptoms resulting in decreased intake for 24-48 hours                                                                                                                                      | Minimal intake for > 48 hours                                                                                                | Hypotensive shock                                           |
| Vomiting                                 | Transient or intermittent vomiting resulting in minimal or no interference with ADL                 | Persistent episodes of vomiting resulting in interference with ADL                                                                                                                                     | Associated with vomiting of all food/fluids in 24 hours and orthostatic hypotension requiring IV fluid/therapy               | Hypotensive shock                                           |

| 2. OTHER SYSTEMIC EVENTS                         |                                                                                                |                                                                                                                                                             |                                                                                                                                                           |                                                                                                                                                   |

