| 24-hour urine                                   |                                   |                                   |                                                       | OR                           |
|                                                 |                                   |                                   |                                                       | > 3.0 g loss/day             |
| HEMATURIA (in the absence of vaginal bleeding)  | 1+ (ca. 5 – 10 Ery/ $\mu$ l)      | 2+ (ca. 10-25 Ery/ $\mu$ l)       | 3+ (ca. 50 Ery/ $\mu$ l)                              | 4+ (ca. 250 Ery/ $\mu$ l)    |
| By microscopic exam only                        | 6-10 Ery/hpf                      | >10 Ery/hpf                       | OR
Gross, with or without clots
OR
RBC casts | Transfusion required         |
| GLUCOSURIA                                      | 1+
(30mg/dl, 2.8 mmol/l)       | 2+
(100mg/dl, 5.5mmol/l)       | 3+
(300mg/dl, 17 mmol/l)                           | 4+
(1000mg/dl, 55 mmol/l) |
| LEUCOCYTURIA                                    | 1+ (ca. 10-25 Leuco/ $\mu$ l)     | 2+ (ca. 75 Leuco/ $\mu$ l)        | 3+ (ca. 500/ $\mu$ l)                                 |                              |

Protocol C001 Amendment – Version 1.1

22 December 03

Appendix C – Adverse Event Grading Toxicity Table Version 31July2003 (Adapted from HVTN/DAIDS Tables, Sept 18, 2002)

UNCONTROLLED COPY

| 4. OTHER CLINICAL OBSERVATIONS |                                                                                                                                              |                                                                                                          |                                                                                         |                                                                                                                   |
|---------------------------------------|----------------------------------------------------------------------------------------------------------------------------------------------|----------------------------------------------------------------------------------------------------------|-----------------------------------------------------------------------------------------|-------------------------------------------------------------------------------------------------------------------|

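### Appendix C's Fahrenheit fever bands leave 102.8°F and 105.0°F in no grade, and its 1+ glucosuria label pairs two concentrations that differ 1.7-fold

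*Protocol*

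**What the plan says.** Appendix C, section 1.2 (systemic reactogenicity) gives each fever grade in both units.

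| Grade | Celsius | Fahrenheit |
|---|---|---|
| Mild | 37.7 to 38.6 | 99.8 to 101.5 |
| Moderate | 38.7 to 39.3 | 101.6 to 102.7 |
| Severe | 39.4 to 40.5 | ">102.8 – 104.9° F" |
| Very severe | above 40.5 | above 105 |

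The grade feeds a primary endpoint. Protocol section 5.1.1 lists "Severe and very severe systemic reactogenicity events (fever, chills, headache, nausea, vomiting, malaise, myalgia" among its components. The same grades decide which vaccine-related events go to the DSMB at interim review (section 16.2.1).

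Appendix C, section 3 (urinalysis) grades glucosuria by a plus reading, with a concentration in each unit in brackets: "30mg/dl, 2.8 mmol/l" for 1+, "100mg/dl, 5.5mmol/l" for 2+, "300mg/dl, 17 mmol/l" for 3+ and "1000mg/dl, 55 mmol/l" for 4+. The test itself is named in Table 3 as "Dipstick: protein, blood, glucose, ketones, esterase (leukocytes), nitrite".

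The document does not say which unit governs either row, or in which unit temperature is recorded.

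**The concern.** A grading table should place every possible reading in exactly one grade, and two columns for the same grade should describe the same range. The fever row fails the first test in Fahrenheit: the strict lower limits for severe and very severe each skip one reading at 0.1-degree resolution. It fails the second because the Celsius entries in the same cells do grade those temperatures.

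What is at stake is how one reading is classified at the line between moderate and severe. A volunteer whose peak is recorded as 102.8°F has no Fahrenheit grade. Someone must choose one, and the choice decides whether the event counts in the severe systemic endpoint or in the mild/moderate proportion. With two sites, the same reading could be handled in two ways.

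The glucosuria pair is a separate and lesser matter. One of four labels gives two concentrations that are not the same quantity.

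**Working it through.** **Fever: the bounds.** The inputs are the limits in the fever row; the formula is °F = 1.8 × °C + 32.

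- Mild, 37.7 to 38.6°C, converts to 99.86 to 101.48°F. Stated: 99.8 to 101.5.
- Moderate, 38.7 to 39.3°C, converts to 101.66 to 102.74°F. Stated: 101.6 to 102.7.
- Severe, 39.4 to 40.5°C, converts to 102.92 to 104.90°F. Stated: strictly above 102.8, to 104.9.
- Very severe, above 40.5°C, converts to above 104.90°F. Stated: strictly above 105.

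The mild and moderate limits reproduce to within 0.1°F. The gaps come from the last two lower limits.

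**Fever: the skipped readings.** Using °C = (°F − 32) / 1.8:

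- 102.8°F: (102.8 − 32) / 1.8 = 39.33°C, recorded as 39.3°C. No grade in Fahrenheit; moderate in Celsius after rounding to one decimal.
- 105.0°F: (105.0 − 32) / 1.8 = 40.56°C, recorded as 40.6°C. No grade in Fahrenheit; very severe in Celsius, rounded or not.

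**Fever: full sweep.** Every 0.1°F reading from 99.0 to 107.0 was graded by the Fahrenheit entries and, after conversion and rounding to 0.1°C, by the Celsius entries. Only 102.8°F and 105.0°F disagree. In the other direction, every 0.1°C reading from 37.0 to 41.9, converted and rounded to 0.1°F, gets the same grade in both columns.

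Rounding matters. The Celsius bands are contiguous only at one decimal, and an unrounded 39.33°C lies between 39.3 and 39.4.

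**Glucosuria.** The conversion factor can be taken from Appendix C itself. In the blood glucose rows of its section 5, mg/dL divided by mmol/l runs from 17.65 to 18.57, and the severe hypoglycaemia cell pairs 30 mg/dL with 1.7 mmol/l. Using 18 mg/dl per mmol/l:

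| Label | Stated mg/dl | Converted, mmol/l | Stated mmol/l | Stated ÷ converted |
|---|---|---|---|---|
| 1+ | 30 | 1.67 | 2.8 | 1.68 |
| 2+ | 100 | 5.56 | 5.5 | 0.99 |
| 3+ | 300 | 16.67 | 17 | 1.02 |
| 4+ | 1000 | 55.56 | 55 | 0.99 |

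Read the other way, 2.8 mmol/l is 2.8 × 18 = 50.4 mg/dl. Three pairs agree within about 2%; the 1+ pair does not.

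**The case against.** The strongest reply is that almost nothing turns on this, and much of that reply stands.

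- **105.0°F.** It lies between severe and very severe. Both grades belong to the same primary endpoint component, and the DSMB reviews them together. Either neighbouring grade gives the same endpoint membership. This stands.
- **102.8°F.** Its Celsius grade depends on rounding to one decimal. This also stands.
- **Investigator judgement.** Section 10.2 makes severity grading ultimately the responsibility of the principal investigator or designee, and Table 4 gives a general principle. This stands in part: such a high fever is unlikely to go ungraded in practice. But section 10.2 extends that principle to events the toxicity table did not foresee, and fever is in the table. Judgement at two sites also does not guarantee one answer for 102.8°F.
- **A typographical slip.** If both strict signs were meant to include the limit, the two gaps close. Then 102.8°F would be severe in Fahrenheit but moderate in rounded Celsius, so the columns would still need reconciling.
- **Glucosuria.** A reader might infer that the choice of unit decides the grade, and with it the mild-event proportion or the mild-laboratory rule in section 12.1. The documents do not support that. Glucose is read by dipstick and graded by the plus reading, so a 1+ is mild whichever bracketed value is read. The mild rule in section 12.1 also turns on the investigator's view of clinical significance. The unit would matter only for results of about 30 to 50 mg/dl graded by concentration, and the protocol schedules no quantitative urine glucose.

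**Conclusion.** The point holds as an error in the grading table, with small practical impact. Two Fahrenheit readings have no grade. One of them, 102.8°F, can change membership of the severe systemic reactogenicity endpoint. That rests on three conditions: temperature is graded in Fahrenheit, it is recorded to 0.1 degree, and the limits are read literally. The conflict with Celsius at 102.8°F further assumes rounding to 0.1°C. The 1+ glucosuria pair is a labelling error that conflicts with the glucose conversion used elsewhere in Appendix C.

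Two stronger readings should be set aside. A reader might infer that the fever gaps bias the severe rate in one direction. They do not: 102.8°F taken as severe would add an event that rounded Celsius calls moderate, while 105.0°F left ungraded would remove one. A reader might also size the problem at 8 percentage points among 12 vaccinees in a dose group (1/12 = 8.3%) or 11 among 9 placebo recipients (1/9 = 11.1%). Those figures are the weight of any single volunteer for any event. They do not measure this defect, and the documents give no basis for how often a peak of exactly 102.8°F would occur.

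**What to change.** Reconcile the Celsius and Fahrenheit entries of the fever row so that every 0.1-degree reading falls in exactly one grade and both units give the same grade. State which unit governs, and how a converted value is rounded. Reconcile the 1+ glucosuria pair so that both bracketed values are the same concentration. Which limits to keep is for the sponsor to decide.

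A programmed consistency check of the fever grade against the recorded temperature may be added. It can support the investigator's grading under section 10.2 and need not replace it.

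The cost is an edit to two rows of Appendix C, circulated to both sites, plus a short database check if wanted. No additional data are needed.

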## 5. ADDITIONAL LABORATORY EVENTS

|                          |                  |                   |                  |                                                                                                           |
|--------------------------|------------------|-------------------|------------------|-----------------------------------------------------------------------------------------------------------|
| HEMATOLOGY        |                  |                   |                  |                                                                                                           |
| Fibrinogen—Elevated      | 450 – 600 mg/dL  | 601 – 650 mg/dL   | > 650 mg/dL      | -----                                                                                                     |
| Fibrinogen-
Decreased | 100 – 200 mg/dL  | < 100 mg/dL       | < 75 mg/dL       | < 50 mg/dL OR
associated with gross bleeding OR associated with disseminated coagulation |
| Prothrombin Time (PT)    | 1.1 – 1.24 x ULN | 1.25 – 1.49 x ULN | 1.5 – 3.0 x ULN  | > 3.0 x ULN                                                                                               |
| PTT                      | 1.1 – 1.66 x ULN | 1.67 – 2.33 x ULN | 2.34 – 3.0 x ULN | > 3.0 x ULN                                                                                               |
| CHEMISTRIES       |                  |                   |                  |                                                                                                           |
| BUN                      | 25 – 30 mg/dL    | 31 – 40 mg/dL     | 41 – 50 mg/dL    | > 50 mg/dL                                                                                                |
| LDH                      | 1.5 – 2.5 x ULN  | >2.5 – 3.5 x ULN  | >3.5 – 5.0 x ULN | > 5.0 x ULN                                                                                               |
| SODIUM                   |                  |                   |                  |                                                                                                           |
| Hyponatremia             | 130 – 135 meq/L  | 123 – 129 meq/L   | 116 – 122 meq/L  | < 116 meq/L                                                                                               |
| Hypertatremia            | 146 – 150 meq/L  | 151 – 157 meq/L   | 158 – 165 meq/L  | > 165 meq/L                                                                                               |

Protocol C001 Amendment – Version 1.1

22 December 03

Appendix C – Adverse Event Grading Toxicity Table Version 31July2003 (Adapted from HVTN/DAIDS Tables, Sept 18, 2002)

UNCONTROLLED COPY

| 5. ADDITIONAL LABORATORY EVENTS                  |                                     |                                      |                                       |                                                               |
|---------------------------------------------------------|-------------------------------------|--------------------------------------|---------------------------------------|---------------------------------------------------------------|
|                                                         | SEVERITY GRADING             |                                      |                                       |                                                               |
| PARAMETER                                        | MILD                         | MODERATE                      | SEVERE                         | VERY SEVERE                                            |
| POTASSIUM                                        |                                     |                                      |                                       |                                                               |
| Hyperkalemia                                            | 5.0 – 5.5 meq/L                     | 5.6 – 6.0 meq/L                      | 6.1 – 6.5 meq/L                       | > 6.6 meq/L                                                   |
| Hypokalemia                                             | 3.2 – 3.4 meq/L                     | 3.0 – 3.1 meq/L                      | 2.5 – 2.9 meq/L                       | < 2.5 meq/L                                                   |
| PHOSPHATASE                                      |                                     |                                      |                                       |                                                               |
| Hypophosphatemia                                        | 2.0 – 2.4 mg/dL                     | 1.5 – 1.9 mg/dL                      | 1.0 – 1.4 mg/dL                       | < 1.0 mg/dL                                                   |
| CALCIUM (corrected for albumin)                  |                                     |                                      |                                       |                                                               |
| Hypocalcemia                                            | 7.8 – 8.4 mg/dL                     | 7.0 – 7.7 mg/dL                      | 6.1 – 6.9 mg/dL                       | < 6.1 mg/dL                                                   |
| Hypercalcemia                                           | 10.6 – 11.5 mg/dL                   | 11.6 – 12.5 mg/dL                    | 12.6 – 13.5 mg/dL                     | > 13.5 mg/dL                                                  |
| MAGNESIUM                                        |                                     |                                      |                                       |                                                               |
| Hypomagnesaemia                                         | 1.2 – 1.4 meq/L                     | 0.9 – 1.1 meq/L                      | 0.6 – 0.8 meq/L                       | < 0.6 meq/L                                                   |
| GLUCOSE                                          |                                     |                                      |                                       |                                                               |
| Hypoglycaemia                                           | 3.1 - 3.6 mmol/l
55 – 64 mg/dL   | 2.2 - 3.0 mmol/l
40 – 54 mg/dL    | 1.7 - 2.1 mmol/l
30 – 39 mg/dL     | < 1.7 mmol/l or mental
status change or coma
< 30 mg/dL |
| Hyperglycaemia
(nonfasting and no
prior diabetes) | 6.5 – 9.0 mmol/l
116 – 160 mg/dL | 9.1 – 14.0 mmol/l
161 – 250 mg/dL | 14.1 – 28.0 mmol/l
251 – 500 mg/dL | > 28.0 mmol/l or
ketoacidosis or seizures
> 500 mg/dL   |
| TRIGLYCERIDES                                    | -----                               | 400 – 750 mg/dL                      | 751 – 1200 mg/dL                      | > 1200 mg/dL                                                  |
| URIC ACID                                        |                                     |                                      |                                       |                                                               |
| Hyperuricemia                                           | 7.5 – 10.0 mg/dL                    | 10.1 – 12.0 mg/dL                    | 12.1 – 15.0 mg/dL                     | > 15.0 mg/dL                                                  |
| LIVER FUNCTION TESTS (LFTs)                      |                                     |                                      |                                       |                                                               |
| GGT                                                     | 1.25 – 2.5 x ULN                    | >2.5 – 5.0 x ULN                     | >5.0 – 10.0 x ULN                     | > 10.0 x ULN                                                  |
| Alkaline Phosphate                                      | 1.25 – 2.5 x ULN                    | >2.5 – 5.0 x ULN                     | >5.0 – 10.0 x ULN                     | > 10.0 x ULN                                                  |
| PANCREATIC ENZYMES                               |                                     |                                      |                                       |                                                               |
| Amylase                                                 | 1.1 – 1.5 x ULN                     | >1.5 – 2.0 x ULN                     | >2.0 – 5.0 x ULN                      | > 5.0 x ULN                                                   |
| Pancreatic amylase                                      | 1.1 – 1.5 x ULN                     | >1.5 – 2.0 x ULN                     | >2.0 – 5.0 x ULN                      | > 5.0 x ULN                                                   |
| Lipase                                                  | 1.1 – 1.5 x ULN                     | >1.5 – 2.0 x ULN                     | >2.0 – 5.0 x ULN                      | > 5.0 x ULN                                                   |

